### Cost-effectiveness analysis

The economic evaluation will be undertaken from a societal perspective. Hence, all relevant effects and costs due to resource utilization within healthcare (direct medical costs) and productivity costs will be included. To examine the cost-effectiveness of the inpatient program compared to the outpatient program the EQ-5D, the SF-6D, and the TiC-P, will be used. We will assess the cost-effectiveness of short-term inpatient DBT compared to outpatient DBT in terms of costs per reduced suicide attempts/self-destructive acts and cost per QALY, the so-called cost utility analysis. The cost utility will be evaluated by relating the difference in direct medical costs per patient receiving inpatient treatment and outpatient care to the difference in terms of QALYs, which yields a cost per QALY estimate. We will estimate the cost per QALY including productivity costs.

The uncertainty will be assessed using bootstrapping, and the results will be presented in acceptability curves.

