Patients also receive daily mindfulness classes, two hours of drama therapy, psycho-educational classes about sexuality, substance abuse and medication, and the possibility of getting help in applying principles of validation and behavioral analysis skills. Other program parts are mainly based on living in a group, such as house-keeping meetings. In order to facilitate skills generalization, patients and staff developed psycho-educational evening sessions (two) in which information on BPD and DBT is given, followed by a training program (six sessions) in which patients together with family and friends can get help in applying skills. Each session lasts two hours. The first two sessions are spent on psycho-education about BPD, DBT and the content of the treatment program. In the next four sessions, all participants are asked to commit to practice the skills that are taught in the program with each other.

During evening and night hours, no staff is present. The results from the data gathered during the developmental phase of the program (October 2009 to September 2011), show that this does not lead to an increase in difficulties in handling relationships.

B) Standard outpatient DBT for 12 months

Patients assigned to standard dialectical behavior therapy receive 12 months of treatment as specified in the DBT manual [16] in one of the three participating regional psychiatric centers of Rivierduinen. The treatment is according to protocol and combines weekly individual cognitive-behavioral psychotherapy sessions with the primary therapist (45 minutes a week, weekly skills-training groups lasting two and a half hours per session (135 minutes), and if needed, consultation and weekly consultation meetings for trainers and therapists (one hour). Individual therapy, in both in- and outpatient programs, focuses primarily on motivational issues, including the motivation to stay alive and to stay in treatment. Group skills training [25] teaches Core Mindfulness skills, Interpersonal effectiveness skills, Emotion regulation skills, Crises skills and Radical acceptance.

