### Objectives

The primary objective is to investigate whether this program is more effective in declining the proportion of patients that show parasuicidal behavior in the first three months of treatment, compared to standard outpatient DBT. We expect that after 12 weeks of inpatient DBT treatment, 20% of the patients will still show suicidal/self-harming behavior (measured by Life Time Parasuicide Count and items of the Borderline Personality Disorder Severity Index) compared to 60% of the patients in standard outpatient DBT. We expect this difference to be sustained after 24 weeks, though it may be reduced between 24 and 52 weeks.

The secondary objectives are: (i) to investigate whether short-term inpatient DBT is more effective in reducing other general (borderline) symptoms, (ii) to investigate whether short-term inpatient DBT is more effective in increasing quality of life, and (iii) to assess the cost-effectiveness of short-term inpatient DBT compared to outpatient DBT in terms of costs per reduced suicide attempts/self-destructive acts and cost per Quality Adjusted Life Year (QALY) from a societal perspective. We expect (i) a stronger decline in Borderline Personality Disorder Severity Index- and Brief Symptomatology Inventory scores and (ii) a stronger increase in quality of life (SF-36 and EQ-5D)-scores in the first three months of inpatient DBT as compared to the control group. We anticipate this difference to be sustained after 24 weeks, though it may reduce between 24 and 52 weeks. We also expect (iii) the initial higher cost of the intensive intervention will lead to better effects and possibly even lower cost than the control condition. Cost savings may be generated in the long run (after one year).

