The *EQ-5D*[46], or *EuroQol 5 Dimensions* descriptive system, is a paper-and-pencil self-report questionnaire that consists of five dimensions (Mobility, Self Care, Usual Activities, Pain/Discomfort and Anxiety/Depression) with three levels each (no problems, some problems and extreme problems), thus defining 243 distinct health states. Each of these health states can be assigned a particular utility using a scoring algorithm. The Dutch tariffs were determined in a time trade-off study. EQ-5D utilities range from −0.329 to 1. Assessment takes one to two minutes.

The *TiC-P* or ‘*Trimbos and iMTA Questionnaire on Costs Associated with Psychiatric Illness*’ (TiC-P) [47] is a validated tool commonly applied in economic evaluations of treatments in mental health care. The TiC-p is a paper-and-pencil self-report questionnaire that consists of two parts. The first part measures direct medical costs. The second part estimates the productivity costs. It includes a short form of the Health and Labor questionnaire (HLQ), consisting of three modules that measure productivity losses: absence from work, reduced efficiency at work and difficulties with job performance [48]. The TIC-P is considered to be a feasible and reliable instrument for collecting data on medical consumption and productivity losses in patients with mental health problems. The construct validity of questions related to contacts with psychotherapist and long-term absence from work is satisfactory [49].

The BSI, or *Brief Symptomatology Inventory* (BSI) [50], is a self-report questionnaire that includes 49 items grouped into nine scales that encompass nine primary dimensions of psychopathological symptoms: psychoticism, somatization, depression, hostility, phobic anxiety, obsessive-compulsivity, anxiety (panic), paranoid ideation, and nervous tension. Derogatis and Melisaratos [50] presented appropriate coefficients of internal consistency of the BSI ranging from 0.71 to 0.85, test-retest reliability coefficients ranging from 0.68 to 0.91, and evidence for the a good construct validity of the BSI. Other studies have reported similar estimates, for example, see references [51,52]. Data of the BSI were collected using a computer-based version.

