However, problems can be expected as a result of the randomization. The fact that allocation of setting is random (outpatient versus inpatient) will create an important toll for participants, because they may be randomized to a treatment condition that was not their primary choice. This involves acceptance of uncertainty. Furthermore, allocation to the experimental program involves an inpatient setting for 12 weeks, which may be difficult to organize for patients with families and work.

Another important problem results from the fact that although an independent, central diagnostic facility was created, the study has no influence on the speed with which patients enter the treatment conditions. The outpatient DBT teams that are part of the trial have a limited capacity and as a result usually have waiting lists.

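### The economic evaluation is called societal but counts only health-care and productivity costs; omitted patient and family costs may bias the cost per QALY in a direction the document does not settle

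*Protocol article*

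**What the plan says.** Under Objectives, the third secondary objective includes "cost per Quality Adjusted Life Year (QALY) from a societal perspective". The Cost-effectiveness analysis section repeats the label, "The economic evaluation will be undertaken from a societal perspective", and draws the cost content from it: "Hence, all relevant effects and costs due to resource utilization within healthcare (direct medical costs) and productivity costs will be included".

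The numerators follow the same two groups. The ratio is introduced on medical costs alone, "The cost utility will be evaluated by relating the difference in direct medical costs per patient receiving inpatient treatment and outpatient care", and then widened: "We will estimate the cost per QALY including productivity costs". No third version is described.

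The TiC-P is the only cost instrument. The Outcomes section describes it in two parts: "The first part measures direct medical costs. The second part estimates the productivity costs".

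Two other places describe demands on families. Under Study conditions, the inpatient programme (and only that programme) includes a "training program (six sessions) in which patients together with family and friends can get help in applying skills". The Discussion says that "allocation to the experimental program involves an inpatient setting for 12 weeks, which may be difficult to organize for patients with families and work".

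**The concern.** A societal perspective is normally understood to include what patients and families bear, not only what the health system and employers bear. The article draws its cost groups as a consequence of the societal label, yet the two groups do not reach that far. The gap also lies in data collection: if the TiC-P gathers only medical and productivity costs, the rest cannot be recovered at analysis.

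This would matter little if the omitted costs were the same in both arms. They are unlikely to be. One arm lives at a unit on weekdays for 12 weeks and has sessions for relatives. The other lives at home and travels to outpatient sessions for a year. The incremental cost, and with it the cost per QALY and the acceptability curve, could then be biased while carrying a label that suggests full coverage.

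**Working it through.** The article states no cost, unit price or cost per QALY, so there is no figure of its own to reproduce. The check has three steps: coverage, direction and sensitivity.

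**1. Coverage**

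| Cost item | In the Cost-effectiveness section? | In the TiC-P as described? |
|---|---|---|
| Health-care use | Yes | Yes (first part) |
| Patient's lost or reduced work | Yes | Yes (second part) |
| Travel to treatment, out-of-pocket costs | No | No |
| Childcare, informal care | No | No |
| Relatives' time, including family sessions | No | No |

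Travel is reimbursed under Ethical precautions, but that is stated together with the voucher for study measurements. It is not a costed item of the evaluation.

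The Discussion names two difficulties with admission, work and families. The productivity part covers the work difficulty; nothing covers the family one.

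**2. Direction of the omitted items**

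*Relatives' session time (inpatient arm only).* Inputs from Study conditions: two hours per session, and either six sessions or two evening sessions plus six. The text is unclear, and its breakdown into two and then four sessions suggests six.
- 6 × 2 = 12 hours; 8 × 2 = 16 hours per attending relative.

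*Admission days.* 12 weeks × 5 days = 60 days away from home. For patients with children, replacement childcare would be higher in this arm. The share of parents is not given.

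*Travel.* Inputs from Study conditions: weekends at home during the 12 weeks, then six months of outpatient treatment, against 12 months of weekly individual and weekly group sessions for controls. Assumptions: one return trip a week during admission; 1 or 2 outpatient visits a week, depending on whether individual and group sessions share a day; six months taken as 26 weeks and 12 months as 52.
- Inpatient arm: 12 + 26 × 1 = 38, or 12 + 26 × 2 = 64 trips.
- Outpatient arm: 52 × 1 = 52, or 52 × 2 = 104 trips.
- Difference: 52 − 38 = 14, or 104 − 64 = 40 more trips for outpatients.

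*Informal care.* The article gives no hours. Controls live at home all week, and the article expects 60% of them still to show suicidal or self-harming behaviour at 12 weeks, against 20% of inpatients. The weekly care spared by admission that would cancel the session hours is session hours × number of relatives / 12 weeks:
- One relative: 12 / 12 = 1.0 to 16 / 12 = 1.3 hours a week.
- Two relatives: 24 / 12 = 2.0 to 32 / 12 = 2.7 hours a week in total.

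Two items therefore add omitted cost to the inpatient arm (session time, childcare), one adds it to the outpatient arm (travel), and one may do so (informal care). Their sum has no determinable sign.

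**3. Sensitivity of the cost per QALY**

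Shift = net omitted cost difference / QALY difference. The QALY gains of 0.05 and 0.10 are assumptions, since the article gives none.
- 500 / 0.05 = 10,000 euros per QALY.
- 500 / 0.10 = 5,000 euros per QALY.

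For scale, the session hours alone, at an assumed 10 to 20 euros an hour, come to 12 × 10 = 120 up to 16 × 20 = 320 euros per attending relative. Taken for one relative and without any offset, that is a shift of 120 / 0.05 = 2,400 to 320 / 0.05 = 6,400 euros per QALY, or 1,200 to 3,200 at a gain of 0.10.

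**The case against.** **The list may not be exhaustive.** The sentence speaks of all relevant costs and does not say only. The article condenses a fuller protocol, where questionnaire additions and unit costs would normally sit. This has some weight: further categories may be planned there. But the article is not silent. It states what is included, presents that as following from the societal label, and describes an instrument with the same two parts. If more is planned, the published definition needs correcting.

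**The omission might be thought to favour the inpatient arm.** A reader might infer this from the family sessions and the 60 admission days. The document does not support it. The control arm has its own omitted costs: more treatment trips on the assumptions above, and possibly more informal care for high-risk patients at home. About one hour of weekly care spared would offset one relative's session time. Attendance by relatives is offered, and full attendance is not stated.

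**The euro figures rest on assumptions.** This is correct. Hourly prices and QALY gains are not in the document. The shift per 500 euros shows how sensitive the ratio is to a net difference of either sign; it does not estimate the bias.

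**The objective is secondary.** Also correct. The primary outcome, the sample size and the clinical analyses are untouched.

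**Conclusion.** The point holds as a mismatch between label and content. The evaluation is described as societal in both Objectives and Cost-effectiveness analysis, but the costs listed and the instrument used cover health care and productivity only. Patient and family costs plausibly differ between arms, so the cost per QALY may be biased. The direction is open, and the plan as described collects no data that would settle it.

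At an assumed QALY gain of 0.05 to 0.10, each net 500 euros omitted moves the ratio by 10,000 down to 5,000 euros per QALY, upward or downward. The trip counts rest on assumed visit patterns and the price range on assumed hourly values. The coverage gap itself rests only on the text.

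**What to change.** - **Collect, in both arms.** Add a few questions on travel to treatment, out-of-pocket costs, childcare or informal care, and relatives' time to the TiC-P at the remaining visits. Family session hours can be taken from the programme schedule and attendance.
- **Report both ways.** Give the cost per QALY and the acceptability curve with and without patient and family costs.
- **Otherwise relabel.** If these costs are not collected, or are incomplete for patients already enrolled, call the analysis a health care plus productivity perspective in Objectives and in Cost-effectiveness analysis. State that patient and family costs are omitted and that the net direction of the effect is unknown. Do not state that the omission favours either arm.

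The cost is a minor respondent burden. Recruitment began in March 2012 and the trial status is recruiting, so visits already completed by early enrollees, possibly including the admission period, would lack the new items. Relabelling costs only wording and a narrower stated perspective.

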**Methods/design:**

Seventy patients, aged 18 to 45 years with a primary diagnosis of BPD, showing a chronic pattern of parasuicidal gestures and/or reporting high degrees of severity of other borderline symptoms, are randomly allocated to the control and intervention groups. Subjects in the control group receive standard outpatient DBT, provided in one of three regular mental health settings in GGZ Rivierduinen. Subjects in the intervention group receive 12 weeks of intensified inpatient DBT plus six months of standard DBT, provided in the Center for Personality Disorders Jelgersma. The primary outcome is the number of suicide attempts/self-harming acts. Secondary outcomes are severity of other borderline complaints, quality of life, general psychopathological symptoms and health care utilization and productivity costs. Data are gathered using a prospective, two (group: intervention and control) by five (time of measurement) repeated measures factorial design.

Participants will complete three-monthly outcome assessments in the course of therapy: at baseline, and 12, 24, 36 and 52 weeks after the start of the treatment. The period of recruitment started in March 2012 and the study will end in December 2014.

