### Sample size

We expect that after 12 weeks, 20% of the patients of the intervention group will still show suicidal and/or self-harming behavior compared to 60% of the patients in the control condition. To be able to detect a difference of 40% after 12 weeks, with a power of 0.80 and an α = 0.05, a minimum of 23 patients per experimental condition is required. We will randomize between approximately 70 patients during the study period to guarantee enough power, taking into account an expected 30% drop-out rate.

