### Randomization

#### Sequence generation

Treatment allocation is carried out by a computer program, developed by the Amsterdam Medical Center. To increase the likelihood of comparable treatment groups, a minimization method is preferred. To preserve the random character of allocation, a biased coin procedure will be used. In case of imbalance, the allocation probability is modified from 50/50 to 80/20. Minimization variables are: level of severity of borderline symptomatology (BPDSI score ≥ 40), level of suicidality/self-harming behavior (LPC score ≥ 14), and age.

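### The cost-per-QALY definition names no adjustment for baseline utility; applied as written, it loses precision and lets chance baseline imbalance into the estimate

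*Protocol article*

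**What the plan says.** All references are to the protocol article.

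- **Estimator.** Under Cost-effectiveness analysis, the cost utility relates the difference in direct medical costs per patient "to the difference in terms of QALYs, which yields a cost per QALY estimate". A second estimate includes productivity costs.
- **Instruments.** The same section states that "the EQ-5D, the SF-6D, and the TiC-P, will be used".
- **Uncertainty.** "The uncertainty will be assessed using bootstrapping, and the results will be presented in acceptability curves". No covariate or baseline term is named.
- **Timing.** The abstract places outcome assessments "at baseline, and 12, 24, 36 and 52 weeks after the start of the treatment", and Study design lists pretreatment as one of the five time points. EQ-5D and the SF-36 (source of the SF-6D) are listed under Outcomes, so by the general schedule baseline utility is collected.
- **Balance.** Under Sequence generation: "Minimization variables are: level of severity of borderline symptomatology (BPDSI score ≥ 40), level of suicidality/self-harming behavior (LPC score ≥ 14), and age". Utility is not among these variables.
- **Other outcomes.** Statistical analysis does give model terms for BPDSI, LPC, SF-36 and BSI: time, condition and their interaction. EQ-5D and QALYs are not in that list.

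**The concern.** A patient's utility at entry usually predicts later utility. If QALYs are computed as an area under the curve, baseline utility also enters the QALY directly. A between-arm QALY difference that ignores it therefore leaves explainable variation in the error. It also passes on any difference in starting utility that chance produces between two arms of about 35.

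The clinical models include the pretreatment time point, so the SF-36 is read against its own baseline. The QALY built from the same questionnaire through the SF-6D gets no such term in the economic section.

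At stake is the precision of the denominator of one of the two economic ratios, and of the acceptability curves drawn from it. The bootstrap shows the uncertainty that an unadjusted difference has. It does not reduce that uncertainty or move the estimate away from an imbalance in the sample actually obtained.

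**Working it through.** **The plan's own figure.** The article states no QALY or utility figure. The only number to carry over is the sample size: "We will randomize between approximately 70 patients during the study period to guarantee enough power". The stated minimum of 23 per arm for 20% versus 60% (power 0.80, α 0.05) reproduces with a two-sided pooled test without continuity correction. Allowing for 30% drop-out, 46 / 0.70 = 65.7, so 66, which about 70 covers. Hence 70 / 2 = 35 randomised per arm, and 35 × 0.70 = 24.5 per arm after drop-out.

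**Assumptions not in the documents.** QALYs by the trapezoidal rule over 52 weeks; the same utility SD at every visit, 0.20 to 0.30; equal correlation r between any two visits, 0.3 to 0.7. As an alternative, correlation that decays serially from 0.5-0.8 per visit step. Complete data unless stated.

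**Step 1: visit weights** for weeks 0, 12, 24, 36, 52. Each is half of the adjoining intervals divided by 52: 6/52, 12/52, 12/52, 14/52, 8/52 = 0.115, 0.231, 0.231, 0.269, 0.154. Their squares sum to 0.216.

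**Step 2: chance imbalance in baseline utility.** SE = SD × √(2/35).
- SD 0.20: 0.048 (1.96 SE = 0.094)
- SD 0.30: 0.072 (1.96 SE = 0.141)

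**Step 3: how much reaches the QALY difference.** Slope of QALY on baseline utility = 0.115 + 0.885r. Shift from a one-SE imbalance = slope × SE.

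| r | slope | shift, SD 0.20 | shift, SD 0.30 |
|---|---|---|---|
| 0.3 | 0.381 | 0.018 | 0.027 |
| 0.5 | 0.558 | 0.027 | 0.040 |
| 0.7 | 0.735 | 0.035 | 0.053 |

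**Step 4: precision.** Var(QALY)/SD² = r + (1 − r) × 0.216. The share of variance removed by adjustment is R² = slope² / [Var(QALY)/SD²]. The proportional cut in SE is 1 − √(1 − R²).

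| r | Var/SD² | R² | SE cut | SE unadjusted → adjusted (SD 0.30) |
|---|---|---|---|---|
| 0.3 | 0.451 | 0.32 | 18% | 0.048 → 0.040 |
| 0.5 | 0.608 | 0.51 | 30% | 0.056 → 0.039 |
| 0.7 | 0.765 | 0.71 | 46% | 0.063 → 0.034 |

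The percentages do not depend on the assumed SD; the absolute figures do.

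**Step 5: sensitivity.**
- Serially decaying correlation (0.5 to 0.8 per step): variance reduction 23% to 56%, which is an SE cut of 1 − √0.77 = 12% to 1 − √0.44 = 34%.
- Drop-out of 30%: absolute SEs and shifts rise by √(35/24.5) = 1.195, about 20%. The percentage gains are unchanged.

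**The case against.** The strongest reply is that the article never calls the QALY difference raw or unadjusted. Its sentence defines an incremental ratio, which an adjusted difference would satisfy equally well. The economic section is two short paragraphs in a journal article, and the covariates of a QALY regression are often left to an analysis plan, which is not shown here. **This stands**: a reader might infer that the plan commits to a crude comparison, and the text does not support that. What remains is that the section sets out numerator, denominator and uncertainty method without a baseline term, while the neighbouring section does give model terms. Applied as it reads, it yields the less precise estimator.

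Three further points from the other side:

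- **No bias.** Over randomisations an unadjusted difference is unbiased, and its sampling error is what the bootstrap and acceptability curves reflect. This stands. The case for adjustment rests on precision and on imbalance in the sample obtained.
- **Minimisation may help indirectly.** If borderline severity and self-harm correlate with utility, balancing them reduces utility imbalance, so the figures above would be somewhat too large. This stands in direction. The size is unknown, and BPDSI and LPC each enter through a single cut-point, so any indirect balance is coarse.
- **Every driving input is assumed.** The article gives only the EQ-5D range; it gives no SD, no correlation and no explicit area-under-the-curve rule. This stands, and is why ranges are shown.

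**Conclusion.** The point holds as an improvement in precision and in protection against chance imbalance; it is not a demonstrated error. Under the stated assumptions, adjusting for baseline utility lowers the SE of the QALY difference by about 18%-46% (variance by 32%-71%), or variance by 23%-56% with serially decaying correlation. A one-SE baseline imbalance otherwise moves the estimate by about 0.02-0.05 QALY with 35 per arm.

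Two stronger inferences should be resisted. A reader might conclude that imbalance could reverse the sign of the QALY difference. The article gives no expected QALY difference against which to judge that. A reader might also treat cost per QALY as the main economic result. Objectives and Cost-effectiveness analysis name it beside cost per reduced suicide attempt or self-destructive act, rank neither first, and place the economic evaluation among the secondary objectives.

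**What to change.** Add one sentence to the economic analysis. The QALY difference is estimated by regressing each patient's one-year QALY on arm and baseline utility from the same instrument (EQ-5D baseline for EQ-5D QALYs, SF-6D baseline for SF-6D QALYs). The regression is refitted within every bootstrap sample, and the adjusted difference is used in the cost-per-QALY ratio and the acceptability curves. Report the unadjusted difference descriptively.

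The cost is that sentence and one regression line in the bootstrap code; no new data, visits or patients are needed. If an analysis plan not shown here already specifies this, the sponsor need only confirm it. Settling it before outcome data are analysed also removes any later choice between adjusted and unadjusted ratios.
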